## Abstract

**Background:**

Spontaneous preterm birth is a complex syndrome with multiple pathways interactions determining its occurrence, including genetic, immunological, physiologic, biochemical and environmental factors. Despite great worldwide efforts in preterm birth prevention, there are no recent effective therapeutic strategies able to decrease spontaneous preterm birth rates or their consequent neonatal morbidity/mortality. The Preterm SAMBA study will associate metabolomics technologies to identify clinical and metabolite predictors for preterm birth. These innovative and unbiased techniques might be a strategic key to advance spontaneous preterm birth prediction.

**Methods/design:**

Preterm SAMBA study consists of a discovery phase to identify biophysical and untargeted metabolomics from blood and hair samples associated with preterm birth, plus a validation phase to evaluate the performance of the predictive modelling. The first phase, a case–control study, will randomly select 100 women who had a spontaneous preterm birth (before 37 weeks) and 100 women who had term birth in the Cork Ireland and Auckland New Zealand cohorts within the SCOPE study, an international consortium aimed to identify potential metabolomic predictors using biophysical data and blood samples collected at 20 weeks of gestation. The validation phase will recruit 1150 Brazilian pregnant women from five participant centres and will collect blood and hair samples at 20 weeks of gestation to evaluate the performance of the algorithm model (sensitivity, specificity, predictive values and likelihood ratios) in predicting spontaneous preterm birth (before 34 weeks, with a secondary analysis of delivery before 37 weeks).

**Discussion:**

The Preterm SAMBA study intends to step forward on preterm birth prediction using metabolomics techniques, and accurate protocols for sample collection among multi-ethnic populations. The use of metabolomics in medical science research is innovative and promises to provide solutions for disorders with multiple complex underlying determinants such as spontaneous preterm birth.

## Background

Despite improvements in antenatal and neonatal care, the number of premature newborns each year has not significantly decreased since the 1960s. Preterm birth (PTB) is the leading cause of neonatal morbidity and mortality and a major contributor to loss of life, long-term disability, and health care costs [1–4]. The associated morbidity, mortality and high health costs have been well documented with premature infants facing life-threatening short and long term complications [5–8].

Despite the enormity of the health economic burden of preterm birth, and many years of focused research, a common aetiology and/or predictive test have not yet been identified. Spontaneous preterm birth (sPTB) is considered one of the “Great Obstetrical Syndromes”, which are conditions resulting from complex interactions between the maternal and fetal genome and the environment and which have a long preclinical period, fetal involvement and adaptive functioning in nature [9]. This reflects the multifactorial nature of this condition and the need to apply strategies that are capable of identifying multiple markers simultaneously in parallel with the assessment of clinical and biophysical risk factors.

There are many clinical [10–13] and biochemical risk factors [14–16] associated with sPTB and it is likely that these biochemical markers are present in the maternal blood long before the onset of a preterm labour. However, although certain candidate-driven approaches to studying these changes show promise, this has not resulted in effective predictive biomarkers for the general pregnant population. Due to these complex and dynamic characteristics of sPTB syndrome, it remains a difficult task to identify women and babies at risk.

Currently, the selection of women likely to deliver prematurely from clinical risk factors alone lacks the sensitivity required to effectively identify the majority of patients at risk of idiopathic sPTB [14]. Furthermore, parameters derived from previous obstetric history cannot be applied to nulliparous women. The association of biophysical predictors such as cervical length and/or vaginal biomarkers (fibronectin and phosphorylated insulin-like growth factor binding protein-1) enhances accuracy for prediction and enables more effective interventions for selected women. There are therapeutic interventions available for the prevention of sPTB, such as the use of progesterone [10, 17, 18] and cervical pessary [19]. Despite advances in selection of eligible women for such therapeutic interventions, the efficacy of cervical length or fetal fibronectin levels in asymptomatic women are still limited and seem to be more capable of discriminating women at lower risk than those at higher risk [20–22]. Owen et al. showed that almost 50 % of women with cervical length between 15 and 25 mm did not deliver before 35 weeks, as well as approximately 70 % with cervical length between 25–30 mm [23].

The development of a predictive test for spontaneous preterm birth would help to accurately identify a high-risk population. To be effective, therapies need to be commenced at a gestational age in which they are likely to be of benefit. A sensitive early pregnancy-screening test would facilitate the timely administration of prophylactic treatments to those women at highest risk. The development of physics, biology and medicine translational research can provide a comprehensive approach for biological processes with complex pathways and regulations. Metabolomics offers an unbiased hypothesis generating approach to identify and validate potential candidate metabolomic biomarkers [24, 25].

We propose a multi-strategy approach to biomarker discovery and validation through the establishment of a large early pregnancy biobank of appropriate samples, in conjunction with the application of analytical methods capable of quantifying multiple blood-borne species simultaneously, and using some clinical and epidemiological markers to identify women at highest risk of spontaneous preterm birth.

The development of predictive tests that translate into clinical care can be divided into two distinct phases; (i) hypothesis generation after acquisition of data, a non-biased process where no or limited biological knowledge is required and (ii) validation of generated hypotheses [26]. The Preterm SAMBA study goal spans both phases and aims to identify a clinically useful early pregnancy-screening test to ascertain which pregnancies are at risk of developing sPTB. Discovery-based methods will be applied to blood and hair samples taken from carefully matched phenotypes in both cohorts (preterm and term deliveries) to develop a predictive algorithm to identify those women at increased risk of sPTB and test the effectiveness of such an algorithm in a prospective cohort.

## Methods/design

Preterm SAMBA, an international collaborative multicentre study for the development of predictive tests that translate into clinical care, can be divided into two distinct phases: The first component (Discovery phase) is a case–control study that aims to identify clinical and metabolomics biomarkers related to spontaneous preterm birth. For this initial phase, untargeted metabolomics techniques will be employed to identify and quantify potential predictor’s metabolites that can be associated to potential clinical predictors. The second component (Validation phase) is a cohort study developed to validate the algorithm of prediction using the clinical and metabolomics biomarkers discovered in the first component of the study. Thus, to evaluate the performance of the prediction model developed at the first phase, targeted metabolomics techniques will be employed to analyse participants’ blood and hair samples to quantify those specific metabolites identified as potential predictors of preterm birth.

### Discovery phase

The initial phase of the project consists of a case–control study utilizing data and samples collected for the SCOPE study (Screening for Pregnancy Endpoints study). The SCOPE consortium was an international effort to determine the causes and potential predictors for pregnancy complications and its methodology had already been previously published [27–29]. Briefly, the cohort comprised 5690 healthy pregnant women recruited between November 2004 and August 2008 in New Zealand, Australia, Ireland and United Kingdom. Inclusion and exclusion criteria for the SCOPE study are described in Tables 1 and 2, respectively. Exclusion criteria include major fetal anomaly, chronic hypertension, diabetes, renal disease, systemic lupus erythematous, and antiphospholipid syndrome. These will therefore be the same criteria for the current study.

**Table 1 Tab1:** Inclusion criteria of Preterm SAMBA validation phase – Brazilian cohort

• Singleton pregnancy	
• Nulliparous (no previous delivery ≥20 weeks)	
• Up to 21 weeks of gestational age

**Table 2 Tab2:** Exclusion criteria of Preterm SAMBA validation phase – Brazilian cohort

• Unsure LMP and unwilling to have dating US	• Major Uterine Anomaly
• ≥3 Miscarriages	• Cervical Suture
• Major Foetal Anomaly/Abnormal Karyotype	• Knife cone biopsy
• Essential Hypertension Treated Pre-pregnancy	• Ruptured membranes now
• Mod-Severe Hypertension at booking (≥160/100 mmHg)	• Long term Steroids
• Pre-pregnancy Diabetes	• Low-dose Aspirin
• Renal Disease	• Calcium (>1 g/24 h)
• Systemic Lupus Erythematosus	• Eicosapentaenoic acid (fish oil)
• Anti-phospholipid Syndrome	• Vit. C ≥1000 mg & Vit. E ≥400 UI
• Sickle Cell Disease	• Heparin/LMW Heparin
• HIV or Hep B or Hep C positive	

Extensive sociodemographic and physical data will be collected including age, ethnicity, socio-economic status, dietary and lifestyle questionnaire, parity, BMI (body mass index) and cigarette smoking.

Plasma and serum samples will be collected at 20 weeks of gestation using stringent standard operating procedures designed for metabolomics studies, barcoded and stored at −80 °C within 2–4 h; the timing between collection and freezing will be known for all specimens.

Several Standard Operating Procedures (SOP) for sample preparation by removal of proteins via ultrafiltration were developed and validated. The analysis of deproteinized plasma samples will be performed employing gas chromatography and liquid chromatography mass spectrometry (GC-MS and LC-MS). GC-MS and LC-MS techniques will be performed as described previously [30, 31]. Quality control samples (acquired by pooling plasma from all subjects) will be interspersed in every 5th run to assess reproducibility and validity. It is envisaged that the socioeconomic/physical/biomarker discovery phase of the Preterm SAMBA study will identify several candidate markers and predictive multivariate models. Discriminatory metabolites will be translated to a targeted triple quad MS (QQQ-MS) platform, to be used in the validation phase.

The proportion of pregnancies complicated by any preterm birth is approximately 10 %. Preterm SAMBA Discovery Phase will randomly select 100 women (*n* = 100) whose pregnancies reached term as compared to fifty randomly sampled pregnancies (*n* = 50) complicated by spontaneous preterm birth prior to 37 weeks gestation, in each of the Cork Ireland and Auckland New Zealand SCOPE cohorts (Fig. 1). The 20th week samples and data will be analysed to identify sPTB potential predictors. Considering there were no previous studies on this topic for preterm birth, these numbers were empirically estimated using a similar study performed for preeclampsia [31]. Using a type I error of 0.01, type II error of 0.10, a ratio between controls and cases of 1:1, an AUC of 0.9 and an OR of 10, the estimated sample of preterm birth is 49. We then anticipated around 50 preterm birth for each of the two centers.

**Fig. 1 Fig1:**
[figure not shown]
Flowchart of Preterm SAMBA Discovery Phase participants (Case-control component)

### Validation phase – the Brazilian multicentre cohort study

The Preterm SAMBA validation phase consists of a Brazilian multicentre cohort study with 1150 low-risk pregnant nulliparous women. Five of the 27 members of the Brazilian Network for Studies on Reproductive and Perinatal Health (BNSRPH), were chosen to participate in the Brazilian cohort (Table 3). Previous excellence performance in epidemiological and translational studies and diversity of cultural, ethnical and sociodemographic population characteristics were criteria for centre selection. Therefore, there are participating centres in three of the five regions of Brazil, which are the three most populated regions of the country: Northeast, Southeast and South.

**Table 3 Tab3:** Participating centres in the Preterm-SAMBA study validation phase – Brazilian cohort

Maternity of CAISM, University of Campinas, in Campinas, São Paulo.	
Maternity of the School of Medicine from UNESP, in Botucatu, São Paulo.	
Maternity of the Clinic Hospital, Federal University of Rio Grande do Sul, in Porto Alegre, Rio Grande do Sul.	
Maternity of the Clinic Hospital, Federal University of Pernambuco, in Recife, Pernambuco.	
MEAC – School Maternity of the Federal University of Ceará, in Fortaleza, Ceará.	

Assuming a type I error rate, α, of 5 % and an estimated area under ROC curve of at least 0.68, then in order to test hypotheses to a suitable level of power (80 % power, β = 0.2), the sample size sufficient should approximate to 80 cases of spontaneous preterm birth (<34 weeks gestation), calculated using MEDCALC®. Based on a minimum expected preterm birth rate of 7 %, the total cohort size should therefore be of approximately 1150 subjects, around 230 women at each participating centres.

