The identification of spontaneous preterm birth predictors using multi-ethnic data/samples and the evaluation of performance in a culturally and ethnically different population is desirable and meaningful for external validation. The use of quality control records and SPREC protocol is another important recommendation for metabolomics studies due to the necessity to evaluate confounders for analytical measures such as the time between sample collection, storage and processing conditions and the occurrence of haemolysis, lipaemia and metabolic degradation on account of inadequate temperature or solar exposure [37].

In the context of translational research, metabolomics may enhance understanding of the underlying pathways, which lead to obstetric complications. Preterm SAMBA aims to identify and validate a predictive model for spontaneous preterm birth, but will also develop a biobank and database that will enable research on pre-eclampsia (PE), fetal growth restriction (FGR) and gestational diabetes mellitus (GDM). The possibility to combine biochemical, genetics and clinical information that can be large-scale and replicable empowers the development of knowledge for clinical practice in preterm birth prevention. This would be especially worthwhile and helpful for countries with a high proportion and high absolute number of preterm births as is the case of Brazil where around 12 % of all births occur prematurely [46].

A recent clustered designed study showed that 30 % of all spontaneous preterm births do not have any maternal, fetal or placental conditions identified that could be related to its occurrence [47]. The application of metabolomics techniques could be a promising approach for spontaneous preterm birth prediction, all the more in those cases of silent phenotype in which there are no known predictors. Metabolomics have been already described in other obstetric conditions as pre-eclampsia, gestational diabetes mellitus and fetal growth restriction [31, 40, 41, 45, 48, 49], showing excellent performance in terms of a discriminatory algorithm. Therefore, we believe metabolomics is a powerful and strategic key not only for preterm birth prediction, but hopefully also for its prevention. The detection of metabolic pathways related to PTB syndrome may enable the development of more accurate therapies for primary or secondary prevention of pregnant women identified as at high-risk.

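### The validation cohort is sized with a 7% preterm birth rate that does not describe the primary outcome, so 1150 women should yield clearly fewer than the 80 spontaneous births before 34 weeks that the protocol says it needs.

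*Protocol article*

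**What the plan says.** The sample-size paragraph of the Protocol article (Validation phase – the Brazilian multicentre cohort study) runs in two steps.

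- **Cases needed.** It starts from "Assuming a type I error rate, α, of 5 % and an estimated area under ROC curve of at least 0.68" with "80 % power, β = 0.2" and concludes that "the sample size sufficient should approximate to 80 cases of spontaneous preterm birth (<34 weeks gestation"). It names no null AUC and does not say whether the test is one- or two-sided.
- **Women needed.** "Based on a minimum expected preterm birth rate of 7" %, it then says that "the total cohort size should therefore be of approximately 1150 subjects, around 230 women at each participating centres".

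Under Postpartum data, the main outcome is spontaneous birth before 34 weeks, through preterm labour or ruptured membranes. Spontaneous birth before 37 weeks and provider-initiated preterm birth are separate secondary outcomes. The Abstract has the same order of primary and secondary.

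The other overall rates in the article are for preterm birth of any kind. The Discovery phase section says "The proportion of pregnancies complicated by any preterm birth is approximately" 10%. The Discussion says that in Brazil about 12% "of all births occur prematurely".

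**The concern.** The two steps use different outcomes. The first counts spontaneous births before 34 weeks. The second divides by a rate called only a preterm birth rate. The primary outcome is a subset of preterm birth in two respects: it drops provider-initiated births and it drops births at 34–36 weeks. The cohort is also described as low-risk, with uterine anomaly, cervical suture and knife cone biopsy among the exclusions, so there is no reason to expect an unusually high rate.

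If the 7% belongs to a broader outcome, the 80 cases do too, and the primary validation will have fewer. The planned performance measures (AUC, sensitivity, specificity, predictive values, likelihood ratio) would then be estimated much less precisely for the primary outcome than the stated 80 cases suggest.

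**Working it through.** **1. Reproducing the plan's figure.** Women = cases / rate = 80/0.07 = 1143, which rounds to about 1150. In reverse, 1150 × 0.07 = 80.5, and 5 centres × 230 = 1150. The arithmetic is right. It yields 80 primary cases only if 7% is the rate of spontaneous birth before 34 weeks.

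**2. Can 7% be that rate?** Set it against the article's figures for any preterm birth:

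- 7/10 = 70% of all preterm births (general figure)
- 7/12 = 58% of all preterm births (Brazilian figure)

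That leaves 30–42% to cover every birth at 34–36 weeks plus every provider-initiated preterm birth.

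**3. Expected primary cases.** The article gives no rate for the primary outcome, so the shares here are assumptions: 60–70% of preterm births spontaneous, and 20–35% of those before 34 weeks. Cases = 1150 × base rate × spontaneous share × share before 34 weeks.

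| Base rate, any preterm birth | Low (0.60 × 0.20) | High (0.70 × 0.35) |
|---|---|---|
| 7% (the plan's rate, read as all-cause) | 9.7 | 19.7 |
| 10% (Discovery phase) | 13.8 | 28.2 |
| 12% (Discussion, Brazil) | 16.6 | 33.8 |

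If 7% already means spontaneous birth before 37 weeks, the count is 80.5 × 0.20 to 80.5 × 0.35, or 16–28. Even if half of spontaneous preterm births came before 34 weeks, a 10–12% base gives 1150 × 0.10 × 0.60 × 0.50 = 34.5 to 1150 × 0.12 × 0.70 × 0.50 = 48.3.

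**4. Precision.** Hanley–McNeil variance for AUC A with m cases and n = 1150 − m non-cases:

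Var = [A(1−A) + (m−1)(Q₁−A²) + (n−1)(Q₂−A²)] / (mn), where Q₁ = A/(2−A) and Q₂ = 2A²/(1+A).

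At A = 0.68: A(1−A) = 0.2176, Q₁−A² = 0.0528, Q₂−A² = 0.0881.

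| Cases | SE | 95% half-width (1.96 × SE) |
|---|---|---|
| 80 | 0.0339 | 0.067 |
| 34 | 0.0514 | 0.101 |
| 14 | 0.0796 | 0.156 |
| 10 | 0.0941 | 0.184 |

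**5. Power.** Two-sided 5%, true AUC 0.68, 1150 women: power = Φ{[(0.68 − A₀) − 1.96 × SE(A₀)] / SE(0.68)}, where A₀ is the null AUC.

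| Cases | A₀ = 0.50 | A₀ = 0.58 |
|---|---|---|
| 80 | >99% | 83% |
| 34 | 94% | 49% |
| 23 | 84% | 35% |
| 14 | 64% | 24% |

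Both nulls are assumptions. With about 13.3 non-cases per case (93/7), 80% power against 0.50 needs only 22 cases, so the stated 80 is not the case count for a null of 0.50 in this design. It corresponds roughly to a null of 0.58, which needs 74 cases.

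**The case against.** The strongest defence is that too few cases need not mean too little power. Against a null AUC of 0.50, about 22 cases suffice, so much of the 14–34 range still has at least 80% power. This stands. A reader might infer from the shortfall that the validation is underpowered, for example at 24–49%. The document does not support that conclusion: those figures depend on a null of 0.58 obtained by solving backwards from 80 cases and 80% power. The defence does not rescue the stated count, though. If 80 cases really are what 80% power requires, as the protocol says, fewer cases miss that target. If the null is 0.50, the 80 was not the requirement.

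A second objection is that 14–34 is not a figure from the document. This also stands. The range rests on assumed shares; the article alone supports only clearly fewer than 80.

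A reader might also conclude that 7% must be the rate of spontaneous birth before 37 weeks, and that the two outcomes should be swapped. The article does not say so. Read literally as all-cause, 7% gives 1150 × 0.07 × 0.60 to 0.70 = 48–56 spontaneous births before 37 weeks, again short of 80. Birth before 34 weeks is consistently the primary outcome, and changing that to suit the sample size would be a design decision, not a correction.

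Finally, the absence of an allowance for lost outcomes is no defect here. A condensed article may leave it to the full protocol, and the point does not depend on it.

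**Conclusion.** The point holds as a mismatch between outcome and rate, not as a calculation error. The 80 primary cases are unsupported, because the rate that produces them is not tied to spontaneous birth before 34 weeks and is not credible for it beside the article's own 10% and 12%. Nothing elsewhere in the article resolves this.

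The size depends on the assumed shares (60–70% spontaneous, 20–35% of those before 34 weeks): roughly one eighth to two fifths of the stated cases (10/80 to 34/80), and an AUC interval about 1.5 to 2.8 times as wide (0.101/0.067 to 0.184/0.067). The widening needs no null value. The effect on power stays undetermined until the null AUC is stated.

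**What to change.** Keep 1150 women and keep birth before 34 weeks as the primary outcome. In the sample-size paragraph:

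- State what the 7% refers to: all-cause or spontaneous, and before which gestational age.
- State an expected rate of spontaneous birth before 34 weeks in this population, with its basis, and replace the 80 cases by 1150 times that rate.
- State the null AUC and sidedness, then give the power or the detectable AUC, and the expected confidence-interval width, for that number of cases.
- If the 7% is the rate of spontaneous birth before 37 weeks, say that the 80 cases belong to that secondary outcome.

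The cost is a change of wording in one paragraph, with no extra women. The only downside is that the stated precision for the primary outcome becomes less favourable. Holding to 80 primary cases instead would require a much larger cohort: 80/0.03 = 2667 women at an assumed rate of 3%, or 80/0.012 = 6667 at 1.2%.
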